## Abstract

**Background::**

The treatment of post-stroke depression (PSD) with anti-depressant drugs is partly practical. Transcranial alternating current stimulation (tACS) offers the potential for a novel treatment modality for adult patients with PSD. In this study, we will assess the efficacy and safety of tACS for treating PSD and explore its effect on gamma and beta-oscillations involving in emotional regulation.

**Methods::**

The prospective study is an 8-week, double-blind, randomized, placebo-controlled trial. Seventy eligible participants with mild to moderate PSD aged between 18 years and 70 years will be recruited and randomly assigned to either active tACS intervention group or sham group. Daily 40-minute, 77.5-Hz, 15-mA sessions of active or sham tACS targeting the forehead and both mastoid areas on weekdays for 4 consecutive weeks (week 4), and an additional 4-week observational period (week 8) will be followed up. The primary outcome is the proportion of participants having an improvement at week 8 according to the Hamilton Depression Rating Scale 17-Item (HAMD-17) score, including the proportion of participants having a decrease of ≥ 50% in HAMD-17 score or clinical recovery (HAMD-17 score ≤ 7). Secondary outcomes include neurological function, independence level, activities of daily living, disease severity, anxiety, and cognitive function. The exploratory outcomes are gamma and beta-oscillations assessed at baseline, week 4, and week 8. Data will be analyzed by logistical regression analyses and mixed-effects models.

**Discussion::**

The study will be the first randomized controlled trial to evaluate the efficacy and safety of tACS at a 77.5-Hz frequency and 15-mA current in reducing depressive severity in patients with PSD. The results of the study will present a base for future studies on the tACS in PSD and its possible mechanism.

Trial registration number: NCT03903068, pre-results.

## Introduction

1

Post-stroke depression (PSD),^[1]^ as a clinical syndrome following brain injury, is the most common complication of stroke and is characterized by prominently depressed mood, markedly diminished interest or pleasure, overwhelmed feeling of isolation and despair.^[1–7]^ The prevalence of PSD is high with approximately one-third of stroke survivors at any one time,^[8]^ spanning from 39% to 52% within the first 5 years.^[9]^ PSD can negatively affect patients, including poor functional outcomes^[3,8]^ and increased mortality.^[3,5,10]^ Some therapeutic options have shown to be effective for PSD, including pharmacological,^[11]^ non-pharmacological interventions especially for late-life depression,^[12]^ and combination therapies.^[11,13–17]^ The most available agents are antidepressants, mainly selective serotonin reuptake inhibitors (SSRIs) and serotonin and norepinephrine reuptake inhibitors (SNRIs).^[14]^ However, those antidepressant agents not only show unwanted side effects, including nausea, diarrhea, fatigue, and dizziness,^[3]^ but also produce a high chance of hemorrhagic complications and stroke.^[18,19]^ Therefore, in addition to antidepressants treating PSD, non-pharmacological interventions have been proposed to treat PSD,^[4,13]^ including transcranial magnetic stimulation (TMS). Since the Food and Drug Administration approved TMS for the treatment of major depressive disorder (MDD) in 2009,^[20]^ the increasing interest in the effect of new non-pharmaceutical therapy for depression has been reported.^[21]^ However, the TMS procedure in different trials not only has paradoxical consequences,^[22]^ but also causes a potential of seizure,^[23]^ as well as has relatively high costs.^[21]^

Transcranial alternating current stimulation (tACS) is a kind of cranial electrotherapy stimulation (CES). Studies revealed that it is a noninvasive, portable, safe,^[24]^ easy to manage, and well-tolerated^[25]^ CES of delivering brain stimulation by applying a low intensity electrical current to the scalp to modulate cortical excitability and spontaneous brain activity.^[26–29]^ Compared with transcranial direct current stimulation (tDCS), tACS has fewer adverse events, and only mild and temporary adverse reactions were reported.^[30]^ Accordingly, it has obtained increasing attention on the effect of regulating brain activity in different participants,^[31,32]^ and has been suggested to treat anxiety, depression, and insomnia.^[23]^ However, there is a lack of robust results available to support the effect of tACS treating patients with post-stroke depression.^[33]^

Regarding the mechanism of tACS modulating brain activity, the published papers showed that tACS may target alpha-, gamma-, and theta- oscillations to play important roles in manipulating brain function. ^[34–37]^ However, studies exploring the application of tACS practices for oscillations-based outcomes in PSD are scarce. The recent report indicated that tACS can treat depressive symptoms by modulating alpha-oscillations in MDD patients.^[37]^ However, to our knowledge, no published reports are assessing the oscillations-based mechanisms underlying the treatment effects of tACS in patients with PSD.

Our preclinical experiment on the effect of tACS at a frequency of 77.5-Hz and 15-mA current treating in depression have shown that tACS has a therapeutic effect via stimulating the forehead and both mastoid areas.^[38]^ Therefore, we hypothesize that tACS at a frequency of 77.5-Hz and 15-mA current may treat patients with PSD. And the proposed study is to explore the efficacy of the tACS at a frequency of 77.5-Hz and 15-mA current in the treatment of depression in PSD participants. The study will provide an alternative approach to treat individuals with PSD.

## Methods

2

### Study design

2.1

This is an 8-week, randomized controlled trial (RCT) aimed to evaluate the efficacy of tACS in treating PSD. Seventy participants with PSD will be recruited from the Department of Neurology, Xuanwu Hospital of Capital Medical University, Beijing, China. After obtaining written informed consent from participants, potential participants will be screened for their eligibility. If eligible, they will be randomized to either the active or sham intervention group with a ratio of 1:1. Participants will undergo a 4-week intervention period (week 4), and another 4-week observational follow up (week 8). Outcomes will be evaluated for all participants at 3 time points: at baseline, at week 4, and week 8. All procedures of this trial will follow the strictly Consolidated Standards of Reporting Trials (CONSORT) guidelines (see Fig. 1) and Standard Protocol Items: Recommendations for Interventional Trials (SPIRIT) Checklist.

**Figure 1 F1:**
[figure not shown]
Flowchart of the study design.

### Recruitment

2.2

Trained investigators will explain the study's objectives, procedures, and possible side effects of participation in detail for each potential participant, who has the right to ask any questions and obtain corresponding answers before he or she makes a decision. After a participant agrees to enroll, a written informed consent form should be obtained, and another copy of the content form will be provided for the participant. Each potential participant will be assessed for his or her eligibility by a trial investigator. If the potential participant is eligible, they will be randomized into tACS or sham treatment. An outline of the procedures is presented in Figure 1. The trial will recruit participants beginning at March 15, 2020, will complete at August 30, 2020.

### Inclusion and exclusion criteria

2.3

A diagnosis of PSD is based on the “Depressive disorder due to another medical condition” of Diagnostic and Statistical Manual of Mental Disorders, Fifth Edition (DSM-V).^[39]^ Inclusion criteria are as follows: aged 18 to 70 years of either sex, right-handed, more than 6 months after the onset of stroke; satisfying with the criteria of major depressive disorder with single episode,^[39]^ the duration of depressive disorder persists for more than two weeks; having the Hamilton Depression Rating Scale 17-Item (HAMD-17) scores higher than 17 at baseline;^[40]^ absence of psychiatric disorder or family history of psychosis before stroke; has never taken antidepressants before enrollment; having the level of audiovisual for examinations required for the study, and providing signed informed consent.

Exclusion criteria include: patients with life expectancy < 6 months; severe or unstable organic diseases, acute brain injury and infection; the impaired skin integrity at the electrode placement site or skin allergic to electrode gel or adhesive; active current suicidal intent or plan as shown by a score of ≥3 on the suicide item of HAMD-17; current participation in any other clinical trial; prior exposure to all kinds of neuromodulation treatments (including electroconvulsive therapy, TMS, tDCS, etc); prior exposure to any implanted device in body (including a cochlear implant, cardiac pacemaker, an implanted device or metal in the brain); a history of brain organic diseases (including seizures, hydrocephalus, and brain tumors), and any situations the investigators believe that they are not suitable for this study.

### Withdrawal and discontinuation

2.4

Participants can freely withdraw the trial at any time. Criteria for the study termination include: severe adverse responses; other diseases for which treatment may affect the assessment of the tACS; absence of two consecutive tACS sessions; nonattendance at weeks 4 and 8; and withdrawal of consent.

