### Intervention

2.5

Participants will be allotted to receive active or sham tACS intervention (Nexalin Technology, Inc., Houston, TX) under the same instructions during all sessions for 4 weeks in addition to their routine therapies (including antiplatelet, lipid-lowering, antihypertensive, or antidiabetic therapy). Two trained nurses will conduct the intervention and instruct participants to receive tACS. Participants will be encouraged to turn off their smartphones, drink water, and relax, even fall asleep. Communication with the trained nurses will be restricted.

Three electrodes will be positioned to the scalp: one 4.45 cm × 9.53 cm electrode will be placed over the forehead (Fpz, Fp1, and Fp2, in the 10/20 international placement system) and two 3.18 cm × 3.81 cm over the mastoid areas. Each participant will receive 20 sessions of intervention in 4 consecutive weeks at the fixed time frame once daily from Monday through Friday, with weekends off. Each session lasts 40 minutes with the default current level of 15-mA and a patented frequency of 77.5-Hz in the active group and no stimulation in the sham group. Then, patients will have another 4 weeks of follow-up.

Participants will be guided to refrain from any antidepressants for treating PSD during the study, and can willingly withdraw from this study at any time and choose any other medical treatments, such as antidepressants, when their depressive symptoms worsen.

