#### Primary outcomes

2.6.1

The primary outcome is the proportion of participants having an improvement at week 8, which includes the response per HAMD-17 defined as a ≥ 50% reduction from the baseline^[41]^ or clinical recovery (score ≤ 7).^[21]^

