### Data monitoring

2.11

The trial will be performed according to the International Conference on Harmonization Guidelines for Good Clinical Practice to assure the rigor of the study. Data will be collected in the paper-based CRFs at baseline, weeks 4 and 8 (Table 1). An independent party approved by the local ethical committees will be responsible for data management. All staff is asked to join in a series of training sessions that will cover communicating with participants on trial, handling assessments, instructing participants to relax and drink water during the tACS intervention, collecting variables, and completing CRF. Data will be entered into the EpiData system by two independent investigators, and double-entry verification will be conducted. Any inconsistent entries will be re-checked with original CRF or investigators’ source data if necessary. Typos will be revised until two entered databases are the same. Auditing will be performed for the trial via frequent visits by two neutral trial monitors who have been appointed by the local ethics committee. The independent statistician will have access to the final trial dataset, including intent-to-treat dataset (i.e. all enrolled participants as belonging to the group they will be randomized into) and per-protocol dataset (i.e. those participants who will complete the trial originally allocated).

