### Statistical analysis

2.14

All data from the study will be analyzed by an independent biostatistician using SAS statistical software, version 9.4 (SAS Institute Inc) and will be considered statistically significant at a *P* value < .05, and all tests are two-sided. Outcomes are based on the intention-to-treat analysis. Missing data will be monitored using the multiple imputation method. Continuous variables will be summarized as mean and standard deviation (SD). Categorical variables will be described as frequency and percentage. Between-group comparisons will be tested by the Mann-Whitney *U* test for continuous variables and the Chi-square test for categorical variables.

The primary outcome will compare the proportion of participants achieving an improvement of depression per HAMD-17 between the 2 groups after 8 weeks of the trial. Secondary outcome analyses will be conducted based on standard statistical principles for comparison of parametric or non-parametric distributions as appropriate. Logistical regression analyses will be utilized to analyze the primary and secondary variables between groups, such as HAMD-17 total score, NIHSS score, mRS score, BI score, CGI-I score, CGI-S score, and epileptic seizure. The secondary outcomes on changes of HAMA, MMSE, MoCA, RBANS, and beta-and gamma-oscillations will be analyzed using mixed-effects models, controlling for time of measurement.

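### Section 2.4 ends study participation, not only stimulation, for missed sessions and clinical events, so week-8 outcomes needed for the intention-to-treat analysis may go uncollected when they could be obtained

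*Protocol article*

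**What the plan says.** Section 2.4 (Withdrawal and discontinuation) opens its list with "Criteria for the study termination include: severe adverse responses; other diseases for which treatment may affect the assessment of the tACS" and continues with "absence of two consecutive tACS sessions; nonattendance at weeks 4 and 8; and withdrawal of consent". All five items have the same stated consequence.

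Four other statements bear on this:

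- Section 2.6.1 sets the endpoint: "The primary outcome is the proportion of participants having an improvement at week 8", judged on HAMD-17.
- Section 2.14 states "Outcomes are based on the intention-to-treat analysis". Section 2.11 describes that dataset as "all enrolled participants as belonging to the group they will be randomized into", and separately a per-protocol dataset of "those participants who will complete the trial originally allocated".
- For gaps in the data, section 2.14 says "Missing data will be monitored using the multiple imputation method".
- Section 2.13 allows for 20% attrition.

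The article does not say that a participant who meets a section 2.4 criterion is still assessed at week 4 or week 8.

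**The concern.** Of the five criteria, only withdrawal of consent by its nature ends the right to collect data. Two missed sessions, a severe adverse response and an interfering disease are post-randomisation events after which a participant may be able and willing to attend the week-8 visit. By placing them in the same list, the plan creates missing primary outcomes that could be avoided, in people whom the intention-to-treat set must contain.

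The reasons for leaving may be informative. Missed sessions can reflect low mood or poor tolerability, and adverse responses could differ between 15-mA stimulation and none. If loss depends on outcomes that were never seen, multiple imputation cannot be relied on to remove the bias. An analysis plan cannot recover data that were not collected.

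Safety is touched as well. Section 2.7 analyses TESS symptoms and seizures at weeks 4 and 8, and those who left because of a severe adverse response may be absent from those assessments.

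**Working it through.** **1. The rule against the endpoint.** Sessions run over weeks 1 to 4: "Each participant will receive 20 sessions of intervention in 4 consecutive weeks". The primary outcome is at week 8. A participant who meets the two-session rule in week 1 would leave about 8 − 1 = 7 weeks before the endpoint. One who meets it at the end of week 4 would leave about 8 − 4 = 4 weeks before. Either way the week-8 HAMD-17 falls after the exit. Sections 2.11 and 2.14 keep the person in the analysis set, so the outcome has to be imputed.

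**2. The plan's own sample size.** Inputs from section 2.13: 50% versus 15%, 80% power, two-sided 5%. The mean rate is 0.325 and the difference 0.35.

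- n = [1.96·√(2·0.325·0.675) + 0.842·√(0.25 + 0.1275)]² / 0.35² = 26.9, so 27 per group. The unpooled formula gives 25. The stated 26 is reproduced to within one.
- Attrition: 26 × 1.2 = 31.2, so 32 as stated (26/0.8 = 32.5 would give 33). The total of 70 is 35 per arm.

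**3. Power with and without the planned loss.** Power = Φ{[0.35·√n − 1.96·√(2·0.325·0.675)] / √(0.25 + 0.1275)}.

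| Participants per arm with an outcome | Power |
|---|---|
| 35 (all assessed) | 89.6% |
| 28 (35 × 0.8, planned 20% loss) | 81.6% |

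The planned loss costs about 8 points of power and still leaves it near 80%.

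**4. How many might meet the two-session rule.** The article gives no miss rate, so the rate q is an assumption. Suppose each of 20 sessions is missed independently with probability q, and a Friday and the following Monday count as consecutive. Let a be the probability of no run of two so far with the last session attended, and b the same with the last session missed. Start at a = 1, b = 0. At each session the new a is (a + b)(1 − q) and the new b is a·q. After 20 sessions the share meeting the rule is 1 − a − b.

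| Assumed miss rate per session | Share meeting the rule | Of 70 |
|---|---|---|
| 2% | 0.7% | about 0.5 |
| 5% | 4.4% | about 3 |
| 10% | 16.1% | about 11 |
| 15% | 31.9% | about 22 |

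If a participant's absences run together in time, the shares would be higher at the same miss rate. The table covers the two-session rule only. The other criteria cannot be sized from the article.

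**The case against.** The strongest reply is that this is loose wording in a condensed article. Section 2.4 never says that assessments stop, and the full protocol may continue them. The analysis plan also anticipates missing data, and section 2.12 describes retention measures (calls before the week-4 and week-8 assessments, a transport allowance). Part of this stands: the lost score is a consequence of the rule as labelled, not something the article states outright. But who stays in follow-up is a rule of conduct that the article does state. If a fuller document continues follow-up, section 2.4 misreports it and still needs correcting.

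A reader might infer more than the text supports:

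- *That the rule contradicts intention-to-treat.* It does not. Terminated participants remain in the set as randomised, imputation is planned, 20% attrition is allowed for, and completers form a separate per-protocol set. The fault is avoidable missingness.
- *That missing any one visit ends participation.* The wording joins weeks 4 and 8 with *and*, so it may mean missing both. Someone absent at week 8 has no week-8 score under any rule. Only an either-visit reading, applied to week 4, would add loss.
- *That starting treatment for any other disease ends participation.* The criterion is limited to diseases whose treatment may affect the tACS assessment, and section 2.5 expressly allows routine therapies.
- *That the loss is known to differ by arm.* No arm-specific adherence is given, both arms have the same schedule, and the introduction reports only mild and temporary reactions. Differential loss is possible, not shown.
- *That the treatment difference is uncertain by some 40 points because of this rule.* With 7 of 35 lost per arm and 14/28 versus 4/28 observed, the extremes are 14/35 − 11/35 = 8.6 points and 21/35 − 4/35 = 48.6 points. Those are worst-case bounds for any 20% loss. Consent withdrawal, including leaving to take antidepressants (section 2.5), and ordinary loss to follow-up would remain after the fix, so the range does not measure this rule.

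**Conclusion.** The point holds as a conduct rule that makes primary outcomes missing when they need not be. Section 2.4 gives adherence and clinical events the same consequence as withdrawal of consent, and no other section restores follow-up. The number affected cannot be known from the article: under independent misses of 5% to 15% per session, about 4% to 32% of participants would meet the two-session rule. That range rests wholly on the assumed miss rate. Power is not the main issue, since 28 per arm still gives about 82%. The main risk is bias from loss that may be related to outcome or arm, whose direction and size the article does not allow one to state.

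**What to change.** Reconcile section 2.4 with sections 2.6.1, 2.11 and 2.14:

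1. Separate discontinuation of stimulation from withdrawal from the study. Which events stop stimulation stays with the sponsor, and no change to those criteria is proposed here.
2. State that every randomised participant who has not withdrawn consent is still sought for the scheduled week-4 and week-8 assessments (at least HAMD-17, concomitant medication and safety) and is analysed as randomised.
3. Clarify whether the visit criterion means missing both visits or either one, and state that a missed week-4 visit does not cancel the week-8 assessment.

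The cost is protocol and CRF wording, plus a few assessments of participants who have stopped stimulation, at visits already planned. The change needs to be in place before participants begin to meet these criteria, because the data cannot be recovered later.

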### Intervention

2.5

Participants will be allotted to receive active or sham tACS intervention (Nexalin Technology, Inc., Houston, TX) under the same instructions during all sessions for 4 weeks in addition to their routine therapies (including antiplatelet, lipid-lowering, antihypertensive, or antidiabetic therapy). Two trained nurses will conduct the intervention and instruct participants to receive tACS. Participants will be encouraged to turn off their smartphones, drink water, and relax, even fall asleep. Communication with the trained nurses will be restricted.

Three electrodes will be positioned to the scalp: one 4.45 cm × 9.53 cm electrode will be placed over the forehead (Fpz, Fp1, and Fp2, in the 10/20 international placement system) and two 3.18 cm × 3.81 cm over the mastoid areas. Each participant will receive 20 sessions of intervention in 4 consecutive weeks at the fixed time frame once daily from Monday through Friday, with weekends off. Each session lasts 40 minutes with the default current level of 15-mA and a patented frequency of 77.5-Hz in the active group and no stimulation in the sham group. Then, patients will have another 4 weeks of follow-up.

Participants will be guided to refrain from any antidepressants for treating PSD during the study, and can willingly withdraw from this study at any time and choose any other medical treatments, such as antidepressants, when their depressive symptoms worsen.

